#### Secondary outcomes.

(1) bilateral sternocleidomastoid and upper trapezius SWE parameters;(2) pain intensity measured by the Faces Pain Scale-Revised (FPS-R);(3) cervical disability measured by the Pediatric Neck Disability Index (Pediatric NDI);(4) cervical rotation range of motion;(5) recurrence-related outcomes at 3 and 6 months after treatment;(6) overall clinical efficacy at week 4.

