### Missing data

Missing data are expected to be limited, with an anticipated missing data rate of approximately 10%, consistent with the dropout allowance used in the sample size calculation. When missing or inconsistent data are identified, the study team will first verify the original case report forms and source documents. Data queries will be generated and resolved by trained study personnel before database lock. If data remain missing, the reason for missingness will be documented whenever possible, including withdrawal, missed assessment, poor ultrasound image quality, inability to complete the assessment, receipt of prohibited co-interventions, or loss to follow-up.

The primary analysis will follow the intention-to-treat principle, with participants analyzed according to their originally assigned groups. The primary ANCOVA will use participants with available baseline and week-4 primary outcome data. If missing primary outcome data are considered likely to influence the results, multiple imputation under the missing-at-random assumption will be performed as a sensitivity analysis. Linear mixed-effects models for repeated secondary outcomes will use all available data under the missing-at-random assumption. No imputation will be performed for adverse events; these will be summarized based on observed data.

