### Statistical analysis

Statistical analyses will be performed using SPSS version 22.0. Continuous variables will be presented as mean ± standard deviation when normally distributed or as median (interquartile range) when not normally distributed. Categorical variables will be presented as frequencies and percentages.

The statistical analysis plan was refined in this manuscript to meet randomized trial reporting standards. The original ethics-approved protocol specified descriptive statistics and pre-post comparisons. The manuscript further specifies baseline-adjusted between-group analysis for the primary endpoint and repeated-measures models for longitudinal outcomes.

The intention-to-treat population will include all randomized participants, who will be analyzed according to their originally assigned groups. The primary ANCOVA will be based on participants with available baseline and week-4 primary outcome data. Multiple imputation under the missing-at-random assumption will be performed as a sensitivity analysis if missing primary outcome data are considered likely to influence the results.

The primary outcome will be analyzed with analysis of covariance, with affected-side sternocleidomastoid stiffness at week 4 as the dependent variable, treatment group as the fixed factor, and baseline affected-side sternocleidomastoid stiffness as the covariate. Adjusted between-group differences with 95% confidence intervals will be reported. To avoid overfitting given the modest sample size, additional covariate adjustment will be limited to prespecified clinically relevant variables. A supplementary adjusted model may include age, sex, baseline symptom duration, and baseline pain intensity, if model assumptions and data completeness permit. These analyses will be considered supportive of the primary baseline-adjusted analysis.

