Repeated secondary outcomes will be analyzed according to their scheduled assessment time points. SWE parameters and cervical rotation range of motion will be assessed at baseline, week 2, and week 4. Pain intensity and cervical disability will be assessed at baseline, week 2, week 4, and at 3 and 6 months after treatment. Recurrence-related outcomes will be assessed at 3 and 6 months after treatment. Linear mixed-effects models will be used for repeated outcomes, with terms for group, time, and the group-by-time interaction, where appropriate. The overall effectiveness rate at week 4 will be compared between groups using the chi-square test or Fisher’s exact test, as appropriate.

The primary outcome will be tested at a two-sided significance level of 0.05 without adjustment for multiplicity. Secondary outcomes will be interpreted as supportive and exploratory. To address potential multiple comparison issues across secondary outcomes, adjusted P values using the Holm-Bonferroni method will be reported where appropriate, together with effect estimates and 95% confidence intervals. Interpretation of secondary outcomes will emphasize the magnitude and precision of treatment effects rather than statistical significance alone.

Model assumptions will be assessed before final interpretation of the primary and secondary analyses. For the ANCOVA model, residual distribution, homogeneity of variance, linearity between the baseline covariate and the week-4 outcome, and influential observations will be examined using residual plots and appropriate diagnostic procedures. For linear mixed-effects models, residual distribution, variance structure, and model convergence will be assessed. If substantial deviations from model assumptions are observed, data transformation or robust standard errors will be considered where appropriate. For the primary outcome, a rank-based ANCOVA adjusted for the baseline value of the primary outcome will be used as a non-parametric sensitivity analysis if the assumptions of the standard ANCOVA are not met. For repeated secondary outcomes, if the assumptions of linear mixed-effects models are seriously violated, transformed outcome models, robust variance estimation, or rank-based repeated-measures approaches will be considered as sensitivity analyses. These alternative analyses will be interpreted as sensitivity analyses, while the prespecified ANCOVA and linear mixed-effects models will remain the primary analytical framework.

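### The mixed models for the repeated secondary outcomes carry no baseline covariate or common-baseline constraint, so their treatment contrasts are less precise than a baseline-adjusted analysis

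*Protocol article*

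**What the plan says.** The Statistical analysis section gives the model for repeated outcomes in one sentence: "Linear mixed-effects models will be used for repeated outcomes, with terms for group, time, and the group-by-time interaction, where appropriate". Just before it, the section says "Repeated secondary outcomes will be analyzed according to their scheduled assessment time points" and sets out those time points: "SWE parameters and cervical rotation range of motion will be assessed at baseline, week 2, and week 4", and "Pain intensity and cervical disability will be assessed at baseline, week 2, week 4, and at 3 and 6 months after treatment". Both lists begin with baseline. The Missing data section adds: "Linear mixed-effects models for repeated secondary outcomes will use all available data under the missing-at-random assumption".

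The primary outcome is handled differently. Its ANCOVA has "treatment group as the fixed factor, and baseline affected-side sternocleidomastoid stiffness as the covariate". The article draws the distinction itself: "The manuscript further specifies baseline-adjusted between-group analysis for the primary endpoint and repeated-measures models for longitudinal outcomes". Baseline adjustment is therefore stated for the primary endpoint, and the longitudinal outcomes get a repeated-measures model with the three terms above.

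The Secondary outcomes list includes "bilateral sternocleidomastoid and upper trapezius SWE parameters", which takes in the affected-side sternocleidomastoid, the primary variable. The article does not say which contrast of the mixed model is the treatment effect for any secondary outcome.

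**The concern.** Read together, these statements describe a model in which baseline is one of the response times and each group has its own free mean at every time, baseline included. Randomization makes the true baseline difference zero, yet the model spends information estimating it. Two week-4 contrasts are then available:

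- the group-by-time contrast, which is the difference between groups in change from baseline;
- the group difference at week 4, which makes no use of the baseline value.

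The first subtracts the whole observed baseline imbalance, more than the correlation warrants. The second subtracts none of it. A baseline-adjusted analysis removes the right share and has the smaller variance whenever the correlation lies strictly between 0 and 1.

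What is at stake is the width of the confidence intervals for pain, disability, rotation and the SWE parameters in a 70-child trial. That matters here because the plan says it will interpret secondary outcomes by the size and precision of effects rather than by significance.

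**Working it through.** **The plan's own figure first.** From the Sample size section: difference 6.5 kPa, SD 9.0 kPa, two-sided 0.05, 80% power, 1:1 allocation. By the normal approximation, n per arm = 2 × [9.0 × (1.960 + 0.842) / 6.5]² = 30.1, rounded up to 31. Allowing 10% loss, 31 / 0.9 = 34.4, rounded up to 35 per arm, or 70 in total. Both stated figures reproduce. They concern the primary outcome only; the article gives no SD, target difference or power for the secondary outcomes.

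**Inputs for the comparison.** Let σ be a common SD at baseline and week 4, n the number per arm, and ρ the baseline-to-week-4 correlation within a child. The article does not give ρ, so a range of 0.3 to 0.8 is assumed. Equal SDs over time are also assumed.

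**Variance of the week-4 treatment contrast (large sample).**

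- Raw week-4 difference: (2σ²/n) × 1
- Group-by-time (change) contrast: (2σ²/n) × 2(1 − ρ)
- Baseline as covariate, or common baseline mean: (2σ²/n) × (1 − ρ²)

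Relative to the adjusted analysis, the variance is 2(1 − ρ)/(1 − ρ²) = 2/(1 + ρ) times as large for the change contrast and 1/(1 − ρ²) times as large for the raw contrast. Interval width goes with the square root.

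| ρ | Variance ratio, change | Interval wider by | Variance ratio, raw week 4 | Interval wider by |
|---|---|---|---|---|
| 0.3 | 1.4/0.91 = 1.54 | 24% | 1/0.91 = 1.10 | 5% |
| 0.5 | 1.0/0.75 = 1.33 | 15% | 1/0.75 = 1.33 | 15% |
| 0.7 | 0.6/0.51 = 1.18 | 8% | 1/0.51 = 1.96 | 40% |
| 0.8 | 0.4/0.36 = 1.11 | 5% | 1/0.36 = 2.78 | 67% |

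The two contrasts fail in opposite directions: the change contrast loses most when ρ is low, the raw contrast when ρ is high. Neither beats the adjusted analysis anywhere in the range.

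**Illustration on a familiar scale.** The primary outcome's SD of 9.0 kPa and 31 per arm are borrowed here only because the secondary outcomes have no figures of their own. The raw standard error is 9.0 × √(2/31) = 2.29 at every ρ.

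| ρ | SE, change | SE, raw week 4 | SE, adjusted |
|---|---|---|---|
| 0.3 | 2.70 | 2.29 | 2.18 |
| 0.5 | 2.29 | 2.29 | 1.98 |
| 0.7 | 1.77 | 2.29 | 1.63 |
| 0.8 | 1.45 | 2.29 | 1.37 |

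**Check with the repeated-measures structure.** Generalized least squares with three time points, 31 per arm and known covariance gives the same standard errors under a constant correlation. At ρ = 0.5 they are 2.286 (change), 2.286 (raw week 4) and 1.980 (common baseline mean). With a correlation that decays over visits (0.7 between neighbours, so 0.7² = 0.49 from baseline to week 4) they are 2.309, 2.286 and 1.993. The week-2 visit does not recover the loss; the baseline-to-week-4 correlation governs it.

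**The case against.** The strongest reply is that the sentence ends with a qualifier about appropriateness, that a detailed SAP is still to be finalized, and that a journal article need not give the full parameterisation. The secondary outcomes are also declared supportive and exploratory, so no confirmatory claim rests on them. The status of the outcomes stands and limits how much this matters. The appeal to the SAP does not carry: the article already names the model terms, treats the mixed models as prespecified, and reserves baseline adjustment for the primary endpoint. The qualifier adds no baseline term.

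Four stronger readings are tempting, and the document supports none of them:

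- **That baseline is ignored.** It is listed as a time point, so the group-by-time contrast does use it, as a change score. It would be ignored only if a raw visit difference were reported or baseline were left out of the response, and the article settles neither.
- **That planned power is lost.** The sample size belongs to the primary outcome, which has a baseline-adjusted ANCOVA. Power figures built from 6.5 kPa and 9.0 kPa describe no secondary analysis in this trial.
- **That every clinical outcome is affected.** The effectiveness rate and recurrence are compared by chi-square or Fisher's exact test.
- **That the primary variable will have two rival answers.** Affected-side stiffness may indeed appear in both the ANCOVA and a mixed model, and the estimates can differ because one uses children with both values and the other all available data. But the plan ranks them: the baseline-adjusted week-4 comparison is primary, and the bilateral SWE data support its interpretation.

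**Conclusion.** The point holds as one of efficiency. With the terms stated, either available treatment contrast for the repeated secondary outcomes is unbiased but less precise than the baseline-adjusted analysis the plan already uses for its primary outcome. Over assumed correlations of 0.3 to 0.8, intervals are about 24% down to 5% wider for the change contrast and about 5% up to 67% wider for the raw week-4 contrast.

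This rests on baseline being a level of time in the response (the natural reading, though not spelled out), on equal SDs over time, and on a correlation range the document does not supply. Because the reported contrast is not named, the actual loss cannot be narrowed further. Nothing here touches the validity of the primary analysis. It is a worthwhile and essentially free improvement.

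**What to change.** In the Statistical analysis section, replace the mixed-model sentence with one of two forms:

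1. post-baseline visits as the response, with group, visit, group-by-visit, the baseline value and baseline-by-visit; or
2. baseline kept in the response with a common baseline mean for both groups, that is, time and group-by-post-baseline time with no group main effect.

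The second fits more closely with the Missing data section's intention to use all available data. In either case, name the baseline-adjusted group difference at week 4 as the reported effect, and the 6-month difference as well for pain and disability.

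Optionally, add that the ANCOVA is the only week-4 between-group estimate reported for affected-side sternocleidomastoid stiffness. Changing the baseline handling would not by itself make the two analyses agree, since they use different sets of children.

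The cost is a sentence or two. The baseline values are already collected, and no visit, sample size or primary analysis changes.

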### Sensitivity analyses

The intention-to-treat analysis will be considered the primary analysis. A per-protocol analysis will be performed as a sensitivity analysis to assess the robustness of the primary findings. The per-protocol population will include participants who complete the week-4 primary outcome assessment, receive at least 80% of the assigned treatment sessions, have no major protocol deviations, and do not receive prohibited co-interventions during the intervention period. Sensitivity will be evaluated by comparing the direction, magnitude, and 95% confidence intervals of the treatment effect between the intention-to-treat and per-protocol analyses. If the results are consistent across these analyses, the findings will be considered robust. If meaningful discrepancies are observed, the potential influence of adherence, missing data, and protocol deviations will be examined and reported.

All tests will be two-sided. A P value <0.05 will be considered statistically significant for the primary analysis. Secondary analyses will be interpreted as supportive and exploratory, with multiplicity-adjusted P values reported where appropriate.

### Patient and public involvement

Patients and members of the public were not formally involved in the design, conduct, reporting, or dissemination planning of this protocol. The intervention schedule and outcome assessment procedures were developed by the clinical and research team on the basis of clinical experience, feasibility, and the published literature. A plain language summary of the study findings will be made available to participating children and their legal guardians on request after completion of the trial.

### Trial status

The ethics-approved Chinese protocol is version 2.0. The submitted English protocol manuscript was prepared as a reporting version based on the ethics-approved protocol. The trial was registered in the International Traditional Medicine Clinical Trial Registry (ITMCTR2025002448) on 27/10/2025. Recruitment began on 27/10/2025 after trial registration had been completed. No participant was enrolled before completion of trial registration. Recruitment is expected to be completed on 31/10/2026. Because recurrence-related outcomes will be assessed at the 6-month follow-up after treatment, data collection is expected to be completed by 31/05/2027.

### Protocol and statistical analysis plan access

The original ethics-approved clinical trial protocol in Chinese is provided as S1 File, and its complete English translation is provided as S2 File. A detailed statistical analysis plan will be finalized, dated, and retained by the investigators before database lock and before the main analysis is performed. The statistical analysis plan will be made available on reasonable request, subject to applicable ethical and institutional requirements.

## Discussion

This trial will evaluate whether adding cervical resistance training to joint mobilization provides greater benefit than joint mobilization alone in children with AARS. The study addresses an important gap in pediatric cervical rehabilitation, because conservative treatment is widely used in clinical practice but structured high-quality randomized evidence remains limited [1,3,8]. The trial also reflects the current emphasis on early conservative management, which is supported by previous pediatric series showing that prompt diagnosis and timely nonsurgical treatment may improve outcomes [30–32]. At the same time, recent reviews indicate that the optimal nonsurgical strategy for pediatric AARS has not yet been clearly established and that delayed presentation may increase the risk of relapse, treatment failure, or subsequent surgical management [33–35].

This protocol has several strengths, including its randomized controlled design, blinded outcome assessment, and a prespecified primary analysis approach. It also uses a single primary imaging endpoint, namely affected-side sternocleidomastoid stiffness at week 4, which may improve interpretability and reduce outcome ambiguity. In addition, musculoskeletal ultrasound and shear-wave elastography provide objective outcome measures and complement standard clinical assessments of pain, disability and range of motion. The detailed intervention protocol may also support reproducibility in future studies and clinical practice.

This protocol also has several limitations. Full blinding is not possible because the two interventions are clearly different. Therapist contact time is greater in the intervention group than in the control group, which may influence non-specific treatment effects. In addition, the trial is conducted at a single center, which may limit generalizability. Ultrasound-based muscle assessment is also operator-dependent, although a predefined standardized scanning protocol will be used. Finally, adherence may vary across participants, particularly with respect to attendance at supervised sessions and compliance with study instructions outside treatment sessions.

Even with these limitations, the trial is expected to provide clinically useful evidence on muscle-focused conservative treatment for pediatric AARS. The findings may also clarify whether ultrasound-based muscle markers can help monitor recovery and guide rehabilitation decisions in this population.
